#### Recruitment of children with HIV

Systematic quota-based sampling by age and sex will be used to recruit 300 children from Parirenyatwa and Harare Hospital HIV clinics. Participants will be recruited sequentially as they attend clinic such that 50 male and 50 female will be chosen for each of three age strata: 8–10.99, 11–13.99 and 14–16.99 years. A maximum of five participants will be enrolled on each day for logistical reasons. The total number of children approached each day will be recorded, irrespective of whether they are subsequently eligible or enrolled to determine the sampling fraction. Written consent will be obtained from children and their guardians. Study processes and procedures will be clearly explained to children and their guardians and they will be given the option to accept or decline to take part in the research. It will also be explained that they are allowed to withdraw from the study at any time, for any reason, without affecting the care they receive from the clinic.

#### Recruitment of children without HIV

Three hundred CWH will be randomly sampled from six government primary and secondary schools in the same catchment area as Parirenyatwa and Harare Hospitals. Younger children (8–12 years) will be selected from primary schools and older children (13–16 years) from secondary schools, with 13 year olds coming from both primary and secondary schools. The number of children selected from each school will be proportional to school size, thereby giving each child equal probability of being sampled. A random number sequence will be generated, and school registers will be used to select participants of similar age and sex as the children with HIV using the same quota-based approach of 50 male and 50 female in each of the three age strata. Guardians of selected school children will be invited to the study clinic to complete the consent process. Consenting participants will have a diagnostic HIV test as part of their assessment. Those testing HIV positive (anticipated to be approximately 2%–3%^44^) will be referred for HIV care.

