### Sample size

The sample size was calculated to detect differences in DXA-measured mean size-adjusted bone BMD Z-scores between children with and without HIV. This study will have 80% power (α 0.05) to detect a 0.23 Z-score difference between 300 HIV-infected and 300 uninfected children, assuming an SD of 1.3. As there were no published studies from low income countries, estimates of the expected difference were taken from a US study of children with HIV aged 7–15 years.^10^ In addition, our study will have 80% power to detect a 4.8% difference in the prevalence low size-adjusted BMD between the two groups. This is a smaller prevalence difference than that detected by the most conservative prevalence estimate of low BMD of 7% from three studies in high-income and middle-income countries.^10–12^

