### Statistical analysis

For continuous variables that are normally distributed, the mean and SD will be presented. For skewed continuous variables, the median and IQR will be presented. Categorical variables will be summarised as frequencies and percentages. The distribution of demographic and clinical variables will be compared between CWH and without HIV using independent sample t*-*tests for means, Wilcoxon rank-sum test for medians and χ^2^ tests for proportions.

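### The uninfected children are a cluster sample from six schools, but the power statement has no design effect and no stated analysis accounts for school

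*Protocol article*

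**What the plan says.** **Sampling.** Under Recruitment of children without HIV, the comparison group "will be randomly sampled from six government primary and secondary schools in the same catchment area" as the two hospitals. (The sentence itself names children with HIV, but the heading and context make clear that the uninfected group is meant.) Numbers per school are proportional to school size, "thereby giving each child equal probability of being sampled". The same paragraph sets quotas of 50 boys and 50 girls in each of three age strata, and takes younger children from primary and older children from secondary schools. Study setting puts the catchment at over 116 primary and 42 secondary government schools. The children with HIV are recruited sequentially at two hospital clinics, so only the uninfected group is clustered by school.

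**Power.** The Sample size section claims "80% power (α 0.05) to detect a 0.23 Z-score difference between 300 HIV-infected and 300 uninfected children", "assuming an SD of 1.3", and adds that "our study will have 80% power to detect a 4.8% difference in the prevalence low size-adjusted BMD between the two groups". It mentions neither an ICC nor a design effect.

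**Analysis.** In Statistical analysis, demographic and clinical variables "will be compared between CWH and without HIV using independent sample" t-tests, with rank-sum and chi-squared tests alongside. The Abstract names linear regression for the mean bone outcomes by HIV status. Statistical analysis says that the baseline Z-scores and prevalences will be compared, and names linear and logistic regression for the risk-factor and change analyses. The listed adjustments are physical activity, calcium and vitamin D intake. School does not appear.

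**The concern.** Sampling a few schools and then children within them gives a mean that varies with which schools were picked as well as which children. Random selection from the registers, and allocation in proportion to size, do not remove that first source of variation. It matters whenever the results are meant to speak for more than those six schools, as they are here: the group stands in for uninfected children of the catchment and feeds the planned reference ranges.

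A within-school correlation is plausible on the protocol's own account. The Introduction names malnutrition, social deprivation and physical activity as influences on musculoskeletal development, and nutrition and socioeconomic status are among the a priori risk factors. All of these can differ between schools.

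At stake are the width of the intervals and the false-positive rate for the primary HIV contrast, and the precision of the uninfected mean and prevalence.

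**Working it through.** **Inputs from the protocol:** 300 per group, SD 1.3, difference 0.23, alpha 0.05 (taken as two-sided), power 80%, six schools. Average cluster size m = 300/6 = 50.

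**Assumed:** ICC of 0.005 to 0.05, because the document gives none; equal cluster sizes.

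**Step 1: the protocol's own figures, without clustering.**
- Naive SE = 1.3 × √(2/300) = 0.1061.
- Detectable difference = (1.960 + 0.842) × 0.1061 = 0.297, not 0.23.
- Power at 0.23 with SD 1.3 is 58%.
- The stated 0.23 is recovered only with SD 1.0: 2.802 × √(2/300) = 0.229, power 80.4%.
- The 4.8-point prevalence difference is recovered with 7% against 2.2% (298 independent children per group, power 80.3%), although 2.2% is not stated.

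So both figures, where they can be recovered, correspond to a design effect of 1. The right baseline for judging clustering at SD 1.3 is 0.297.

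**Step 2: add the clusters, in the uninfected group only.**
- Design effect: DE = 1 + (50 − 1) × ICC.
- SE = 1.3 × √((1 + DE)/300); ratio to the naive SE = √((1 + DE)/2).
- Type I error of the naive test = 2 × [1 − Φ(1.96/ratio)].
- Detectable difference at 80% power = 2.802 × SE.

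| ICC (assumed) | DE | Effective n, uninfected | SE ratio | Type I error | Detectable difference, SD 1.3 |
|---|---|---|---|---|---|
| 0 | 1.00 | 300 | 1.00 | 5.0% | 0.297 |
| 0.005 | 1.245 | 241 | 1.06 | 6.4% | 0.315 |
| 0.01 | 1.49 | 201 | 1.12 | 7.9% | 0.332 |
| 0.02 | 1.98 | 152 | 1.22 | 10.8% | 0.363 |
| 0.05 | 3.45 | 87 | 1.49 | 18.9% | 0.444 |

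Example at ICC 0.02: DE = 1 + 49 × 0.02 = 1.98; SE = 1.3 × √(2.98/300) = 0.1296; ratio = √(2.98/2) = 1.22; detectable difference = 2.802 × 0.1296 = 0.363.

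**Step 3: few clusters.** The table uses normal quantiles. With six schools the clustered variance has about 5 degrees of freedom. The Satterthwaite value for the difference is (1 + DE)² / (1/299 + DE²/5), about 14, 11 and 8 at ICC 0.01, 0.02 and 0.05. Using t quantiles with these, the detectable differences become about 0.36, 0.40 and 0.50.

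**Step 4: sensitivity.**
- If SD 1.0 was what the calculation really used, power at 0.23 falls from 80% to 71%, 64% and 47% at ICC 0.01, 0.02 and 0.05.
- If six means six of each school type (12 schools, m = 25), DE is 1.24 to 2.20 for ICC 0.01 to 0.05, and type I error is 6.4% to 12.1%.
- Allocation in proportion to school size makes clusters unequal, which tends to raise the design effect somewhat.

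**Step 5: the equal-probability sentence.** Allocation in proportion to school size would give equal probability if children were then drawn without further restriction. Fixed quotas of 50 per age-sex cell make the probability depend on how many enrolled children fall in each cell. The split by school level changes it again, with 13-year-olds drawn from both. The sentence therefore does not hold as a general statement.

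**The case against.** **The analysis may not ignore school.** Only the descriptive comparisons are explicitly of the independent-sample kind. For the primary outcomes the text says that groups will be compared and names linear regression; robust errors or a random effect would fit under that label and could sit in an analysis plan that is not shown. This stands in part: a reader might infer that the primary contrast is definitely analysed as if children were independent, and the document does not say so. But a later model cannot repair the power statement, which is made for this design and counts 300 independent uninfected children.

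**The harm depends on an unknown ICC.** This stands. At 0.005 the standard error grows by only 6%. Age- and sex-specific, size-adjusted Z-scores also remove part of the between-school variation, though not what comes from deprivation or diet. A reader might conclude that the standard errors are certainly too small, or by a known amount; the document supports neither.

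**The missed precision has another cause.** A reader might blame the schools for the whole distance from the stated 0.23 to 0.33 or more. That would be wrong: the step from 0.23 to 0.297 arises under full independence, from a difference and an SD that do not fit together.

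**Equal probability and reference ranges.** The quotas are stated openly in the same paragraph, and the clinic group uses the same ones, so unequal probabilities across cells do not bias the age- and sex-matched contrast. The Discussion already says that the representativeness of the uninfected children is unknown and describes the reference data as first steps. Both points stand, though a caveat about representativeness does not deal with variance.

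**Conclusion.** The concern holds in a conditional form. The design is a two-stage sample of six schools with about 50 children each; the power statement makes no allowance for it, and no stated analysis does either. If the ICC is above 0 and school is ignored, uncertainty is understated. Over an assumed ICC of 0.005 to 0.05, with the design effect in one group only, the correct standard error is 6% to 49% above the naive one, type I error is about 6% to 19%, and the detectable difference at SD 1.3 rises from 0.297 to between 0.315 and 0.444, or more once the small number of schools is allowed for. These figures rest on the assumed ICC, equal clusters, six schools in total, and inference to the catchment and not just to the six schools. The 0.23 against 0.297 discrepancy is a separate error. The equal-probability sentence is a minor wording fault.

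**What to change.** 1. State how school is handled in the HIV contrast, the change analyses and the uninfected estimates: either a partially nested model (random school intercept in the uninfected group only) or cluster-robust errors, in each case with a small-sample correction. School fixed effects will not work, because school is nested within HIV status.
2. Keep each child's school identifier from the registers in the analysis data set. The questionnaire and Table 1 mention only school attendance.
3. Report the ICC with its uncertainty; with six schools it will be poorly estimated.
4. Restate the detectable differences for means and prevalence under a stated ICC range, after resolving the separate mismatch between 0.23 and SD 1.3.
5. Minor: limit the equal-probability statement to within age-sex cell and school level, and only if allocation is proportional to enrolment within each cell.

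**Cost:** wording and a change of model, with no extra data collection if school identity is kept. The price is wider intervals and few degrees of freedom.

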### Study procedures

#### Questionnaire

An interviewer-administered questionnaire together with hand-held medical records will be used to collect sociodemographic details and clinical history including age, sex, school attendance, orphan status, guardianship, history of fractures with mechanism of trauma, steroid use, smoking, alcohol, recreational drugs, family history of musculoskeletal disease, comorbidities, physical activity, diet and nutrition, and sun exposure. Where possible, validated instruments adapted for the local context will be used. For example, the International Physical Activity Questionnaire (IPAQ)^45^ validated in multiple countries including South Africa and will be used to assess physical activity as multiples of the resting metabolic rate (MET) in MET-minutes. Diet and nutrition will be assessed using a tool we developed for the Zimbabwean context based on a validated dietary diversity and food frequency tool from India and Malawi^46^ and international guidelines applicable to SSA.^47^ The tool quantifies vitamin D supplementation and sunlight exposure and has been adapted to reflect the Zimbabwean context where fortification of oils and margarine with vitamin D is mandated by the government and specific vitamin D–rich foods such as kapenta fish are found.

#### Clinical examination

A standardised musculoskeletal examination will be conducted using the validated paediatric Gait, Arms, Legs and Spine (pGALS) examination.^48^ Additional clinical assessments will be carried out using standardised protocols and calibrated equipment. Anthropometry measurements will include standing and sitting height, arm span and mid-upper arm circumference. Height will be measured to the nearest 0.1 cm, by two separate readers using calibrated Seca 213 stadiometers. If the two height measurements differ by more than 0.5 cm, a third reading will be taken.^49^ Weight will be measured to the nearest 0.1 kg using calibrated Seca 875 scales. Tanner pubertal staging will be carried out using a standardised protocol with an orchidometer to assess testicular volume in male participants.^50^ Muscle function will be assessed in the upper and lower limbs by grip strength dynamometry and standing long jump, respectively. Hand grip strength will be measured using a Jamar hydraulic hand-held dynamometer (Patterson Medical, UK) to the nearest 0.1 kg. Participants will be seated with the shoulder at 0° to 10°, the elbow at 90° of flexion and the forearm positioned neutrally. Three measurements will be taken from each hand in alternation and the highest measurement chosen. The standing long jump distance will be taken from the best of three correctly performed attempts to the nearest 0.1 cm, measuring the distance from the take-off line to the heel.

#### Radiological assessments

DXA scans will be performed by two trained radiographers using a Hologic QDR Wi densitometer with Apex software V.4.5. Measurements will be taken from the lumbar spine, hip and total body. Fat and muscle mass will also be acquired; muscle mass is the fat-free mass measurement from DXA. DXA scans will be repeated in a subgroup (n=20) of participants to determine reproducibility. pQCT measurements of the non-dominant tibia will be taken using a Stratec XCT-2000 scanner (Stratec, Pforzheim, Germany) software V.6.20. Measurements of the non-dominant tibia will be taken at three sites at 4%, 38% and 66% of the tibial length, measured from the medial malleolus to the medial tibial plateau. Daily quality control will be performed by scanning the manufacturer-provided lumbar spine phantom for DXA and tibia phantom for pQCT. A radiograph of the non-dominant hand and wrist will be taken and used to quantify bone age using the Greulich and Pyle (G&P) atlas and the Tanner Whitehouse 3 (TW3) method. For intraobserver reliability, 10% of the radiographs will be randomly selected and rescored by the same operator after 1 week. For interobserver reliability, a different set of 10% of the radiographs will be rescored by a different expert. The estimated bone age will then be compared with the calculated chronological age.

#### Blood tests

A fasting blood sample (up to 15 mL) will be collected. HIV markers (CD4 count and viral load) will be tested in CWH only. CD4 cell count will be measured using an Alere PIMA CD4 machine (Waltham, Massachusetts, USA). HIV viral load will be measured using the GeneXpert HIV-1 viral load platform (Cepheid, Sunnyvale, California, USA). The remaining blood plasma will be biobanked to enable future measurement of bone biochemistry. After removing the plasma, peripheral blood mononuclear cells will be isolated and cryopreserved. DNA will also be extracted using a manual method and stored for future genetic studies.

#### Follow-up at 1 year

All study measurements, with the exception of DNA extraction, will be repeated after 1 year. Participants will be recalled exactly 1 year after their first DXA scan. The aim is to perform all scans within a 4-week window period. Contact will be maintained with participants via regular phone calls and text messaging to minimise loss-to-follow-up. The schedule of study procedures is summarised in table 1.

**Table 1 T1:** Summary of study measurements to be quantified at baseline and follow-up

	Measurement	Measurement method	Outcome
Interview-based questionnaire	Sociodemographic characteristics	Questionnaire	Age, sex, school attendance, orphanhood, guardianship
	Clinical history	Questionnaire*	History of fractures and trauma (modified Landin classification^55^) HIV history: age at diagnosis, WHO disease stage, nadir CD4 count, opportunistic infections† ART regimen/duration† Exposures: steroid use, smoking, alcohol, recreational drugs Family history of musculoskeletal disease and fractures Other comorbidities
	Physical activity	The International Physical Activity Questionnaire (IPAQ)^45^ questionnaire (short form)	Median MET-minutes‡ of physical activity/week Inactive (<600 MET-minutes/week) Minimally active (600–1499 MET-minutes/week) Highly active (≥1500 MET-minutes/week)
	Nutrition‡	Dietary assessment tool (Modified Short Food Frequency Questionnaire^46^)	Daily dietary calcium and vitamin D intake Prevalence of vitamin supplementation Sun exposure
	Quality of life and disability	Washington Disability Score^56^	Functioning and disability score
Standardised examination	Musculoskeletal examination	Paediatric Gait, Arms, Legs and Spine (pGALS)^48^ ±regional clinical examination	Joint, spine and gait abnormalities
	Pubertal stage	Tanner’s staging^57 58^	Prepubertal (stage 1) Pubertal (stage 2–3) Postpubertal (stage 4 and 5)
	Anthropometry	Height (standing and sitting) Weight Mid-upper arm circumference (MUAC)§	Standing height-for-age (Z-score)¶^59^ Weight-for-age (Z-score)¶^59^ Body mass index (BMI) (Z-score)¶^59^ MUAC (Z-score)¶^59^
	Muscle strength	Jamar dynamometer standing long jump¶	Hand grip strength (kg, Z-score)¶^60^ Jumping distance (cm, Z-score)**^61^
Radiology	Skeletal maturity	Hand/wrist radiograph	Bone age (years)
	Bone and muscle composition	Dual-energy X-ray absorptiometry (DXA) of total body, lumbar spine and hip††	Size corrected DXA measures of TBLH BMC^LBM^ (g), LS BMAD (g/cm^3^) and Z-scores <−2.¶ Lean mass
	Bone architecture	Peripheral quantitative computed tomography (pQCT)	Trabecular and cortical vBMD (g/cm^3^), total and cortical CSA (mm²), cortical thickness (mm), periosteal and endosteal circumference (mm), SSI (mm^3^), PMI (mm^4^) and CSMI (mm^4^)
Blood tests	Bone markers and DNA	Blood test (DNA extraction and serum saved)	Future testing e.g. Vitamin D, alkaline phosphotase, C-terminal telopeptide (CTX)‡‡
	HIV markers	Blood test	CD4 count, HIV viral load†

*Details of treatment and comorbidities will be confirmed by patient-held medical records where available.

†Denotes assessments to be carried out in HIV-infected participants only.

‡Energy requirements defined in METS (multiples of the resting metabolic rate that give a score in MET-minutes).

§Nutritional indicator to include composite information from history (usual diet last month, sun exposure–vitamin D status) and clinical examination (MUAC). Similar methods have been used in other low-income contexts.^46^

¶Age-specific and sex-specific Z-scores for (1) anthropometric measures will be determined using the WHO child growth standards.^59^ (2) Hand grip strength will be determined with reference to the uninfected comparison group and European normative data.^60^ (3) Jumping distance will be determined using normative data from South Africa.^61^ (4) Low BMD will be determined with reference to published paediatric Hologic DXA reference databases for LS BMAD and TBLH BMC^LBM^ Z-scores.^36^

**Standing long jump; the longest distance after two attempts will be recorded.

††Pregnancy urine dipstick in female participants prior to DXA if uncertain pregnancy status.

‡‡Tests to be carried out on stored blood when further funding is secured.

CSA, cross-sectional area; CSMI, cross-sectional moment of inertia; DXA, dual-energy X-ray absorptiometry; LS BMAD, lumbar spine bone mineral apparent density; PMI, polar moment of inertia; SSI, Strength Strain Index; TBLH BMC^LBM^, total-body less-head bone mineral content for lean mass adjusted for height.

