## Methods and analysis

### Study objectives

This study aims to determine the impact of HIV infection on size-adjusted bone density in peripubertal children aged 8–16 years established on ART. In addition, this prospective study aims:

To quantify the prevalence of low size-adjusted BMD and low muscle function (grip strength and standing long jump) among CWH compared with uninfected children.To investigate the risk factors for low size-adjusted bone density and low muscle function (grip strength and standing long jump) among CHW.To compare the rates of bone mass accrual over 1 year between children with and without HIV and assess for interaction by pubertal stage to determine if CWH exhibit catch up growth.To determine the differences in bone architecture measured by pQCT between children with and without HIV.

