### Outcome measures

The primary study outcomes are as follows:

Mean size-adjusted bone density Z-scores; TBLH BMC^LBM^ and LS BMAD.^36^
The prevalence of low TBLH BMC^LBM^ and LS BMAD Z-score<−2 at baseline.^36^

Secondary study outcomes are as follows:

Prevalence of low muscle function; grip strength and standing long jump-for-age (Z-score<−2) and musculoskeletal abnormalities/disabilities by HIV status at baseline.Mean percentage change in TBLH BMC^LBM^ (g) and LS BMAD (g/cm^3^), tibial cortical and trabecular volumetric BMD (g/cm^3^), total cross sectional area, cortical thickness and bone strength, muscle mass and function at baseline and 1 year, by HIV status.Assessment of the extent to which pubertal delay explains changes in these bone and muscle outcomes.

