Baseline mean TBLH BMC^LBM^ and LS BMAD Z-scores and the prevalence of low TBLH BMC^LBM^ and LS BMAD Z-score will be compared between CWH and without HIV. Among CWH, the association between a priori defined risk factors (ART duration, ART type, proportion of life on treatment, age at ART initiation, CD4 count, viral load, bone age, pubertal stage, nutrition, socioeconomic status and orphanhood) against size-adjusted BMD will be examined using multivariable linear regression (Z-score as a continuous variable) and multivariable logistic regression (as defined by the Z-score cut-off of <−2). Successful antiretroviral therapy will be defined as a viral load of less than 1000 copies/mL. Paired sample t-test or non-parametric Wilcoxon test will be used to assess for differences in TBLH BMC and LS BMAD on children with and without HIV between baseline and follow-up. Multivariable linear regression will be used to analyse the mean percentage change in TBLH BMC^LBM^ (g) and LS BMAD (g/cm^3^) between children with and without HIV. Models will be adjusted for physical activity, calcium and vitamin D intake. Interaction between the effects of pubertal stage (bone age) and HIV on change in TBLH BMC^LBM^ and LS BMAD will be investigated to see if differences in bone density become more or less pronounced through puberty, that is, whether catch-up growth is possible, see figure 2. The regression coefficient (β) for percentage change in size-adjusted bone mass may suggest either no growth impairment (figure 2A), delayed puberty while maintaining the same growth trajectory (figure 2B) or delayed puberty with a reduced growth trajectory (figure 2C) in CWH. If β is markedly more positive in CWH, this suggests that catch-up growth may be possible (figure 2D). Pubertal delay in this study will be defined as the lack of the initial signs of puberty (Tanner stage 2) at an age that is more than 2 SD beyond the population mean^51^ and as chronological age minus bone age >2 years.^52^ Data for total body and lumbar spine DXA, tibial pQCT, hand grip strength and standing long jump in CWH will be analysed with reference to the comparator group of children without HIV.

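### Bone accrual is to be compared as a rate, but the planned percentage change is neither annualised nor adjusted for actual scan interval, so any difference in mean interval by HIV status would bias the comparison.

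*Protocol article*

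**What the plan says.** All references are to the protocol article.

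- **Study objectives.** The longitudinal aim is "To compare the rates of bone mass accrual over 1 year between children with and without HIV", with an assessment of interaction by pubertal stage to judge catch-up growth. The Discussion also promises growth velocity data.
- **Follow-up at 1 year.** "Participants will be recalled exactly 1 year after their first DXA scan". The next sentence reads: "The aim is to perform all scans within a 4-week window period". It is not said whether the four weeks are a total width or apply on each side of the anniversary, or how a scan outside them is handled.
- **Outcome measures.** The secondary longitudinal outcome is mean percentage change, by HIV status, in the two size-adjusted DXA measures, the pQCT measures, and muscle mass and function. No division by elapsed time is mentioned.
- **Statistical analysis.** "Multivariable linear regression will be used to analyse the mean percentage change in" the two DXA measures between the groups. The covariates follow: "Models will be adjusted for physical activity, calcium and vitamin D intake". The interval between scans is not among them. A markedly more positive coefficient in children with HIV is to be read as possible catch-up growth.
- **Recruitment.** For children with HIV: "Participants will be recruited sequentially as they attend clinic". Children without HIV are sampled from the registers of six schools.

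**The concern.** A rate needs a time base. Percentage change between two visits equals an annual rate only if every child is rescanned at one year. Otherwise a child seen later has had longer to grow and shows a larger change without accruing bone any faster.

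Scatter in timing that is the same in both groups does little harm. A difference in mean interval between the groups is another matter, because it goes straight into the estimated HIV effect and no covariate named in the model would absorb it. By design, HIV status coincides with recruitment source (hospital clinic or school), so any timing difference linked to source would fall wholly on the HIV comparison.

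At stake is the catch-up question. The analysis reads meaning into a larger or smaller change in children with HIV, and later or earlier return of one group would move that quantity in the same way.

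**Working it through.** The article gives no figure for one-year change or for visit timing; its sample size calculation concerns differences in mean Z-score and in prevalence of low BMD. There is therefore no stated figure to reproduce.

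**Inputs from the article:** recall at one year for everyone; a four-week window stated as an aim; 300 children per group.

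**Assumptions:** annual gain *g* of 5 to 10%, the same in both groups; SD of percentage change 4 to 8 points; 240 to 300 children per group at follow-up; change roughly linear over the interval. *w* is the difference in mean interval between the groups, in weeks.

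**Step 1: bias.** Spurious difference = *g* × *w* / 52. Each week contributes 1/52 = 1.9% of the annual gain.

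| *w* (weeks) | Share of annual gain | *g* = 5% | *g* = 10% |
|---|---|---|---|
| 0 | 0 | 0 | 0 |
| 1 | 1.9% | 0.10 points | 0.19 points |
| 2 | 3.8% | 0.19 points | 0.38 points |
| 4 | 7.7% | 0.38 points | 0.77 points |

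The result scales with the gain. If size adjustment brings the annual gain down to 2%, four weeks gives 2 × 4/52 = 0.15 points.

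**Step 2: ceiling.** If the window is four weeks in total and every scan falls inside it, the group means can differ by at most four weeks, and only if the groups sit at opposite ends. A difference of one or two weeks is a more realistic case to plan for.

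**Step 3: false-positive rate with no true difference.** With SE = SD × √(2/n) and b = *g* × *w* / 52, the two-sided rejection rate is Φ(b/SE − 1.96) + Φ(−b/SE − 1.96).

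- Most favourable corner at *w* = 4: SD 8, n = 240, *g* = 5%. SE = 0.73, b/SE = 0.53, rate 8.2%.
- Least favourable corner at *w* = 4: SD 4, n = 300, *g* = 10%. SE = 0.33, b/SE = 2.36, rate 65.4%.
- Over the whole assumed range, the nominal 5% becomes 5.2 to 9.1% at one week, 5.8 to 21.8% at two weeks and 8.2 to 65.4% at four weeks.

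**Step 4: effect on a real difference (illustration).** Suppose true annual gains are 9% in children with HIV and 10% in the comparison group, a contrast of 1.00 point. If the children with HIV are scanned four weeks later on average, their observed gain is 9 × 56/52 = 9.69%, and the contrast shrinks to 0.31. If the comparison group is four weeks later, its gain is 10 × 56/52 = 10.77%, and the contrast grows to 1.77.

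**Step 5: timing scatter unrelated to group.** Intervals spread uniformly over ±2 weeks add an SD of *g* × (2/52)/√3 = 0.11 to 0.22 points and no bias. Against an SD of 4 points, √(4² + 0.22²) = 4.006, a rise of less than 0.2%. Loss of precision is not a reason for the change.

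**The case against.** The strongest objection is that nothing in the article points to unequal timing. One recall rule, tied to each child's own first DXA, one window and one method of keeping contact (calls and text messages) apply to everybody. The groups differ in where they are recruited, not in how they are recalled; even at enrolment, guardians of school children are invited to the study clinic. If recall works as written, percentage change over the year is the annual rate, and objective and outcome agree.

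A reader might infer more: that unequal visit timing will show up as a difference in accrual, or that out-of-window scans are to be counted. The article supports neither. The first needs a systematic group difference in timing that is nowhere stated or implied. On the second the text is silent.

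It can also be said that the covariate list is not declared exhaustive, that a condensed article may leave the use of scan dates to a fuller analysis plan, and that the assumed gains come from no passage and may be too high for size-adjusted measures.

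Most of this stands, and it makes the point conditional and modest. It does not remove it. The article itself fixes the outcome scale and names the adjustment set. As written, neither uses elapsed time, while the objective is a rate and the window is only an aim.

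**Conclusion.** The point holds as a conditional weakness in a secondary analysis. If mean scan intervals differ by HIV status, the accrual comparison is biased by about 1.9% of the annual gain per week, and the sign depends on which group returns later. The bias is zero if the mean intervals are equal and small at one week. At four weeks, which is the limit when a four-week total window is fully met, it is large enough to alter the reading on catch-up growth. The percentage-point sizes rest on assumed annual gains, and the error rates also on assumed SDs and follow-up numbers; the share per week needs only roughly linear change. The primary comparisons, made at baseline, are not touched. This is a cheap improvement to a stated model, not a demonstrated error in the result.

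**What to change.** In the Statistical analysis section, state that the baseline and follow-up scan dates will be used either to express each child's percentage change per year (change divided by the actual interval in years) or to enter the interval as a covariate. Apply the same choice to the DXA, pQCT and muscle change outcomes, taking the dates of the relevant measurements, and report the distribution of the interval by HIV group.

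The cost is a few words of analysis text. Recall is keyed to the date of the first DXA, so that date has to be on record, and no new data should be needed. The downside is that annualising assumes roughly linear change over the interval. That is reasonable for departures of a few weeks and less secure for a child who returns very late.
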